#### Pre-baseline

The PI reviews the documents and confirms the eligibility for the study candidate. An Actiwatch-Score (hereafter referred to as Actiwatch-S; Phillips Respironics, Bend OR), a wrist-worn accelerometer, and a study log book along with instructions are mailed to them. An Actiwatch-S is a wristwatch-like device that continuously measures activity levels and also allows for input of fatigue severity scores. The device is worn by the participant throughout the study period. The study log book accompanies the Actiwatch-S and has additional questions about activity and sleep quality to be completed within and across days in the study. The participants enter their fatigue scores in the log book as they do in the Actiwatch-S, which provides a cross-validation of the time-stamped fatigue entries. The participants are instructed to wear the Actiwatch-S for one week prior to the Baseline Visit and to record their fatigue three times a day at pre-scheduled times after hearing an audible alarm. Prior to the Baseline appointment, the participant is randomized into one of the three arms.

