#### Visit 2- baseline visit (week 0)

At the visit participants fill out questionnaires as indicated in Table
2. If the participants are randomized into one of the acupressure treatment arms, they are given acupressure instructions by the study nurse. A DVD, a handout describing acupressure, and illustrations of the proposed acupressure points are also given to the participants. On this visit the participant returns the Actiwatch-S and the study logbook. The data from the Actiwatch-S are downloaded and the watch is reinitialized and given to the participant along with a new log book.

**Table 2 T2:** Study Visits

	**Visit 1**	**Daily**	**Visit 2**	**Visit 3**	**Visit 4**	**Weekly Phone Calls**	**Visit 5**
	**Screening (within 60 days of baseline)**	**Days (−7 to 70)**	**Baseline Week 0**	**Week 3**	**Week 6**	**Week (−1, 1–2, 4–5 & 7–9)**	**Week 10**
Laboratory Values ^1^	X						
Medical Exam/History/Socio-demographics	X						
Urine Pregnancy Test ^1^	X						
PRIME-MD^2^	X						
HADS ^2^	X				X		X
BFI ^2^	X		X	X	X	X	X
Concomitant Medication & Supplements	X						
Sleep Diary	X				X		
Group Randomization ^3^			X				
Actiwatch Data Collected		X	X^4^	X^4^	X^4^		X^4^
LTQL			X		X		X
BSAPQ ^2^	X		X		X		X
GSE ^2^			X		X		X
BPI^2^	X		X		X		X
Study Logbook		X	X	X	X		X
PSQI ^2^	X				X		X
VAS for Pain ^2^	X						
Berlin Questionnaire	X						
Therapy Evaluation Questionnaire			X		X		
Perform Acupressure ^5^			X	X	X		
Assess Treatment Fidelity – Self efficacy Measure				X	X		
Adverse Events				X	X	X	X
Assessment of Blinding					X		

^1^ Complete Blood Count; blood for correlative tests, blood for future DNA analysis, Urine pregnancy test as appropriate.

^2^ HADS = Hospital Anxiety Depression Scale; BFI = Brief Fatigue Inventory; and PSQI = Pittsburgh Sleep Quality Index; LTQL = Long Term Quality of Life Instrument; BSAPQ = Breast and Surrounding Areas Pain Questionnaire; GSE = General Self Efficacy Scale; BPI = Brief Pain Inventory; VAS for Pain = Visual Analog; PRIME-MD = *Primary Care Evaluation of Mental Disorders.*

^3^ Participants are randomized to one of three treatments: Standard of Care; Relaxation Acupressure; or Stimulating Acupressure.

^4^ Data file downloaded at these visits.

^5^ Does not apply to standard of care arm.

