#### Weekly phone calls (weeks 110)

Participants are contacted once per week to administer the BFI questionnaire, ask about any medical concerns, change in medications, and any questions regarding sleep diary, study log book, acupressure or Actiwatch-S.

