## Statistical issues

### Statistics and power analysis

Primary Aim: The primary aim of this study is to investigate the differential effects of different modes of acupressure on fatigue in breast cancer survivors. For this, we are focusing on three fatigue outcomes, namely, BFI, which will be administered weekly, a measure of average daily physical activity and a self-reported fatigue score, both based on Actiwatch-S data. A BFI is collected weekly and provides a measure of average degree of fatigue, a score that ranges between 0 and 10, with higher numbers indicating more fatigue. We will be analyzing the BFI outcome over phases. The first phase BFI is obtained by averaging week-1 to week-3 measures (mid-treatment). The second phase comprising of week-4 to week-6 measures indicates the status in the second half of the treatment phase (end-treatment). The final phase comprises of week-7 to week-10, the washout phase (washout). In order to investigate the change in BFI between the three study arms, we are using a mixed-effects regression analysis with average BFI in the three phases as the outcome, phase as the within-subjects factor, and group (RA, SA, standard of care) as the primary between-subjects factor. The baseline BFI level will be used as a covariate. We shall further adjust the model for key demographic variables such as age and ethnicity, as well as the baseline HADS score. A *subject* random-effect will be used to account for the clustering effect within the three measurements on the same subject. Of primary interest is the group*phase interaction, the significance of which will indicate differences in extent of decrease between the arms. Post-hoc analyses of phase difference within each arm will be carried out multiple comparison adjustment. Model diagnostics will be carried out to confirm the distributional assumptions and appropriate corrective actions (e.g. transformation) will be performed as needed.

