#### Power analysis

Our power analysis is based on our primary aim of comparing fatigue as measured by BFI across the three study arms.

We compute the power via simulation using a mixed effects model with a between-subject factor group (3 levels), a within-subject factor phase (2 levels), group*phase interaction and a random subject effect. The mean BFI values at mid-treatment were assumed to be 4, 3, 3, respectively for standard care, SA and RA arms whereas the means were taken to be 4, 3, 2 at the end-treatment point in the same arms. The between-subject variance is assumed to be 4 at all time-points whereas the variance of the random subject component is taken to be 4 also (yielding an intra-class correlation of 0.5). These assumed values are estimates based on our pilot data. For this configuration, the power for detecting the difference between groups is more than 0.95 and the power for detecting a significant phase*group interaction is 0.82 with a sample size of 100 per treatment arm and a 5% level of significance. In the second model discussed in the analysis section with phase comprising of end-treatment and washout, if we assume the washout point BFI values to be 5, 4, 3, in the standard care, SA, and RA arms, respectively, the power for detecting either the phase effect or group effect are both around 99%.

We also have powered the study to allow us to observe differences in sleep parameters. The extent of overlap between fatigue and sleep disturbances in BC survivors is currently unknown. Research indicates that 51% of BC survivors experience sleep disruptions and 19% meet diagnostic criteria for insomnia
[35]. While fatigued women are most likely enriched with individuals experiencing sleep disturbances we will conservatively assume that roughly 51% women will have some significant sleep disturbances and 19% will have insomnia per treatment arm. As such, with 100 women per treatment group we will be overpowered for detecting a difference in fatigue and sufficiently powered to detect changes in key sleep measures. For example, using the PSQI as a basis for powering differences in sleep quality from previous studies the mean PSQI in BC patients ranges from 6.84 ± 0.376 to 7.16 ± 0.325.(60,74) A 1 point decrease in the PSQI from ~7 to ~6 is considered clinically significant in this population

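### Averaging the week -1 and week 0 BFI readings as the baseline covariate would tighten between-arm BFI differences at almost no cost; it would not help the group*phase test

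*Protocol article*

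**What the plan says.** The primary model (Statistics and power analysis) takes phase means of weekly BFI as its outcome: "The first phase BFI is obtained by averaging week-1 to week-3 measures (mid-treatment"), then weeks 4 to 6 and weeks 7 to 10. On baseline it says "The baseline BFI level will be used as a covariate" and names no week. The effect of interest follows: "Of primary interest is the group*phase interaction".

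Table 2 marks three BFI assessments before treatment: screening (within 60 days of baseline), the week -1 call, and Visit 2. Visit 2 is the baseline visit, both in the Table 2 column head and in its own section heading ("Visit 2- baseline visit (week 0").

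The weekly-call section says "Participants are contacted once per week to administer the BFI questionnaire", but its heading covers weeks 1 to 10 (the dash is lost in the text at hand). The week -1 call therefore appears only in Table 2.

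The Pre-baseline section adds: "Prior to the Baseline appointment, the participant is randomized into one of the three arms". Table 2 marks randomization at Visit 2.

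**The concern.** Each outcome is a mean of three or four weekly readings, while the covariate is apparently one reading. A single weekly score carries week-to-week noise that weakens its correlation with the outcome, so the adjustment removes less variance than it could. A second reading close to the start of treatment is already scheduled but has no stated role.

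At stake is the precision of between-arm BFI differences, within a phase or averaged over phases. They matter because every modelled phase comes after baseline. An advantage over standard care that is constant from the first phase on appears in the group term, not in the interaction. The trial's hypothesis is also comparative: relaxation acupressure (RA) against stimulating acupressure (SA) and standard of care.

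**Working it through.** **Inputs (Power analysis section).** "The mean BFI values at mid-treatment were assumed to be 4, 3, 3, respectively for standard care, SA and RA arms"; at end-treatment 4, 3, 2; subject variance 4 and a second component of 4 (intra-class correlation, ICC, 0.5), read here as residual variance 4; 100 per arm; 5% level.

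**The plan's own figures.**
- Group effect: two-phase means 4, 3, 2.5 have sum of squares about their mean 1.167. Non-centrality = 100 × 1.167 / (4 + 4/2) = 19.4, giving power 0.98. This agrees with the stated value of more than 0.95.
- Interaction: changes 0, 0, -1 have sum of squares 0.667. Non-centrality = 100 × 0.667 / (2 × 4) = 8.33, giving power 0.73 against the stated 0.82. That gap is a separate matter and is not used here.

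**Effect on the interaction.** The change between phases removes the subject effect and any covariate that is constant over time, so its variance is 2 × 4 = 8 whatever the baseline. In a mixed-model fit to one simulated data set, the interaction standard error was 0.3796 with no baseline, with one reading and with the mean of two. With a baseline-by-phase term added, simulated power was 0.742 (one reading) and 0.743 (two).

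**Effect on a between-arm difference in one phase.** With subject variance s, baseline residual w per reading, k readings and phase residual e:

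adjusted variance = s - s²/(s + w/k) + e

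With s = w = e = 4:
- k = 1: 4 - 16/8 + 4 = 6.00; SE = √(2 × 6.00/100) = 0.346
- k = 2: 4 - 16/6 + 4 = 5.33; SE = √(2 × 5.33/100) = 0.327
- Variance cut 11%; SE cut 5.7%.

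For the mean of the two treatment phases (e/2 in place of e), the variance falls from 4.00 to 3.33 (17%) and the SE from 0.283 to 0.258.

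**Other readings of the variances.** The article does not say whether 4 is the residual of a weekly score or of a phase mean.

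| Assumption (100 per arm, one phase) | SE, one reading | SE, two | Change |
|---|---|---|---|
| Residual 4 per phase mean, 12 per weekly reading | 0.374 | 0.358 | -4.4% |
| Residual 4 per phase mean and per reading | 0.346 | 0.327 | -5.7% |
| Residual 4 per weekly reading, 4/3 per phase mean | 0.258 | 0.231 | -10.6% |
| Subject 7, residual 1 (ICC 0.875) | 0.194 | 0.171 | -11.5% |

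**By assumed weekly ICC, independent weekly errors, three-week phase mean, total variance 1.** Adjusted variance = ICC + (1 - ICC)/3 - ICC²/(ICC + (1 - ICC)/k).
- ICC 0.5: 0.417 to 0.333 (-20%)
- ICC 0.7: 0.310 to 0.224 (-28%)
- ICC 0.8: 0.227 to 0.156 (-31%)

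**With first-order autocorrelated errors** (assumed correlation 0.3 to 0.5, ICC 0.5 to 0.7), the cut is 2% to 14% for weeks 1-3 and 6% to 16% for weeks 4-6.

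**What this means for RA versus SA** (s = w = e = 4, 100 per arm, two-sided 5%). At end-treatment (difference 1), power rises from 0.82 to 0.86. For the two-phase mean (difference 0.5), it rises from 0.42 to 0.49. The 0.82 here only coincides with the article's interaction figure.

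**The case against.** **The primary test gains nothing.** A reader might infer that precision on the primary outcome as a whole is lost. The documents do not support that: the test of primary interest is the interaction, where the covariate drops out, and the named post-hoc contrasts (phase differences within each arm) are also within-woman. This stands in full and limits the point to between-arm differences.

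**Baseline BFI has a natural meaning.** A reader might call the covariate undefined, or fear that the screening value will be used, up to 60 days old and selected by the entry rule of BFI ≥ 4. Visit 2 is labelled baseline and has its own BFI mark, so week 0 is the natural reading and screening is not. The word is used loosely nearby, however: the same model adjusts for baseline HADS, and the sleep analysis uses baseline PSQI, yet before treatment Table 2 marks both only at screening. One clarifying sentence is still worth having.

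**An article may leave derivations to a fuller document.** That is fair, and a single week 0 covariate is valid and unbiased. The point is a proposed gain, not an error.

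**Power is already high.** The stated figure above 0.95 is for the overall three-group test. It does not cover RA versus SA, where there is room to gain.

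**Table 2 governs the calls.** The Study measures section sends the reader to Table 2 for timing, so one cannot conclude that sites will skip the week -1 call. The mismatch is editorial but real.

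**Randomization timing.** The proposed mean still includes a week 0 reading that may follow allocation. This is true, and equally true of week 0 alone; the change does not settle it.

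**Conclusion.** The point holds as a small, nearly free improvement. Table 2 provides two BFI readings close to the start of treatment, the analysis most naturally uses one, and the call-section heading omits the other.

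Using both cuts the adjusted variance of a between-arm difference in one phase by about 11% under the article's variances. The range is 20% to 31% with independent weekly errors and an assumed ICC of 0.5 to 0.8, and about 2% to 16% with the autocorrelation assumed above. The article gives no week-level variance or autocorrelation, so these ranges are assumptions; weekly fatigue scores may well be autocorrelated, so the upper figures should not be relied on. The calculation also ignores the age, ethnicity and HADS adjustments.

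The group*phase interaction is unaffected, and no bias is claimed.

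**What to change.** 1. In the primary analysis, define baseline BFI as the mean of the week -1 and week 0 readings, or the available one if only one exists, and state that the screening BFI is not used as the covariate.
2. Apply the same definition to the baseline severity status in the BFI ≥ 6 analysis and to the BFI change-scores from baseline, so that one definition serves throughout.
3. Align the weekly-call section with Table 2 so that it includes the week -1 call.

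The cost is a sentence or two of analysis wording and a corrected heading. Table 2 already schedules the reading, so participants have nothing extra to do. The definition should be fixed before outcome data are seen by arm. Reconciling the Pre-baseline text with Table 2 on when randomization occurs is a separate correction, but it would show which readings precede allocation.

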Two types of fatigue-related measures will be collected from the Actiwatch-S. The first is a daytime activity count per minute, which is calculated by dividing the total daily activity counts by the total daytime minutes. For each phase as defined above, we shall use the corresponding 21-day (or 28-day) average as appropriate. The second type of measure is obtained from the four self-reported readings of the VAS-F. The daily averages are obtained from the non-missing entries each day, and are then combined to provide the phase average the same way as the daytime activity count. The analytical framework is identical to that for BFI, albeit with the changed outcome.

A secondary analysis with BFI will also be carried out which investigates the difference in proportion of severely fatigued subjects (BFI ≥ 6) across the three study arms. The analytical framework will be that of a mixed-effects logistic regression model with severe BFI (yes/no) being the dichotomous outcome. Apart from group, phase, and group*phase interaction as primary covariates, the model will also be adjusted for baseline status of severity. Remaining covariates in the model are identical to those in the continuous BFI model. The clustering effect due to subject will be accounted for using a generalized estimating equations approach.

In order to assess the extent of association between the improvement in FACT-B and improvement in fatigue measure (specific aim #1 letter D), we shall create the change-scores (week 6 – baseline, week 10 – baseline) for FACT-B (both total and component scores), and BFI. Then we shall fit a linear mixed model similar to that for the original BFI analysis, with BFI change-score as outcome, and the FACT-B change-score as a time-varying covariate. There will not be any phase or week variable in the model. We shall restrict this analysis to the SA and RA arms only so that the group variable will consist of two levels. A group*FACT-B interaction in the model will investigate any differential association across the arms between the change-scores. The additional covariates and clustering adjustment would be similar to the BFI analysis.

Secondary Aims:

1. Assessing difference across study arms with respect to sleep parameters

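### Baseline BFI enters the primary model without a phase interaction, so with complete data it does not act on the group*phase test; adding baseline*phase is a cheap, optional improvement

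*Protocol article*

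**What the plan says.** All of this is in the Protocol article, Statistics and power analysis, under the primary aim, unless another section is named.

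- The model is a "mixed-effects regression analysis with average BFI in the three phases as the outcome, phase as the within-subjects factor", with study arm as the between-subject factor. All three phases (weeks 1-3, 4-6 and 7-10) lie after baseline.
- A subject "random-effect will be used to account for the clustering effect within the three measurements on the same subject". This is one random intercept per woman.
- "The baseline BFI level will be used as a covariate". Age, ethnicity and baseline HADS are further adjustment variables. No purpose is stated for any of them, and no covariate-by-phase term is mentioned.
- "Of primary interest is the group*phase interaction, the significance of which will indicate differences in extent of decrease between the arms".
- For daytime activity and VAS-F: "The analytical framework is identical to that for BFI, albeit with the changed outcome".
- The Power analysis section powers both the group effect (more than 0.95) and the interaction (0.82) at 100 women per arm. Its model lists no baseline covariate.

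**The concern.** A reader will take the primary analysis to be adjusted for baseline fatigue. The test named as primary compares arms on differences between a woman's own phases. A covariate that is constant within a woman and has one slope for all phases drops out of those differences. The baseline score is collected and placed in the model, but with complete data it does no work on the test that matters most.

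Two modest things are at stake. If baseline predicts change between phases, some precision is left unused. In that case a chance baseline imbalance between arms also passes into the interaction estimate, as the imbalance multiplied by the difference in slopes. If baseline does not predict change between phases, neither applies.

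**Working it through.** **1. Algebra.** For woman i in arm g and phase j, the model as described is

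y_ij = μ + γ_g + π_j + (γπ)_gj + β·b_i + u_i + e_ij.

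The difference between phases 2 and 1 is

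y_i2 − y_i1 = (π_2 − π_1) + (γπ)_g2 − (γπ)_g1 + e_i2 − e_i1.

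Both β·b_i and u_i have gone. Age, ethnicity and HADS are also constant within a woman and cancel in the same way. If the slope may differ by phase, (β_2 − β_1)·b_i remains, and baseline then acts on the contrast.

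**2. The plan's own figure.** The assumed means are: "The mean BFI values at mid-treatment were assumed to be 4, 3, 3, respectively for standard care, SA and RA arms"; and "the means were taken to be 4, 3, 2 at the end-treatment point in the same arms". The mid-to-end falls are therefore 0, 0 and 1. I take the subject variance as 4 and the residual variance as 4, the only reading that gives the stated intra-class correlation of 0.5. The variance of a within-woman difference is then 2 × 4 = 8. The noncentrality at 100 per arm is

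λ = 100 × [(1/3)² + (1/3)² + (2/3)²] / 8 = 66.67 / 8 = 8.33.

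With 2 and 297 degrees of freedom at the 5% level, power is 0.73, against the stated 0.82. At 125 per arm (the randomisation target of 375 in three arms) it is 0.83. The stated figure rests on 100 simulations, so its rough 95% interval is 0.74 to 0.90. The mismatch is a separate matter; 0.73 serves here only as the starting value.

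**3. Numerical check of the cancellation.** Random-intercept models were fitted by REML to two simulated data sets with three phases, 100 women per arm, total variance 8 and correlation 0.5 between phases. The baseline-phase correlations are assumptions: 0.50 with every phase in set A, and 0.60/0.45/0.30 in set B.

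| Complete data | No baseline | Baseline main effect | Baseline*phase |
|---|---|---|---|
| A: interaction F | 2.5611 | 2.5611 | 2.634 |
| A: interaction SE | 0.386 | 0.386 | 0.387-0.388 |
| A: group-contrast SE | 0.376 | 0.337 | 0.337-0.338 |
| B: interaction F | 3.6624 | 3.6624 | 3.887 |
| B: interaction SE | 0.386 | 0.386 | 0.381 |
| B: group-contrast SE | 0.400 | 0.360 | 0.358-0.359 |

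The interaction estimates and SEs in the first two columns agree to five decimals. In set B the extra term lowers the interaction SE by about 1.4%.

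With dropout added, the main effect does move the interaction F: 2.06 to 1.92 in set A and 3.21 to 3.49 in set B.

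**4. Size of the possible gain.** With equal variances, the share of the mid-to-end contrast's variance removed by baseline*phase is

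gain = (r_be − r_bm)² / [2(1 − r_me)],

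where b, m and e are baseline, mid-treatment and end-treatment. The protocol's intra-class correlation gives r_me = 0.5, so the denominator is 1. The baseline correlations are not in the document; the ranges are assumed.

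- Equal correlations: gain 0.
- r_bm = 0.60, r_be = 0.55: 0.05² = 0.25%.
- r_bm = 0.70, r_be = 0.40: 0.30² = 9%.

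If r_me were 0.70-0.75 instead of the protocol's 0.5, the same ranges would give 0.0025/0.60 = 0.4% up to 0.09/0.50 = 18%.

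**5. In terms of power.** Let r be the correlation of baseline with the mid-to-end change, so that gain = r². Replace 8 by 8(1 − r²) in step 2.

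| r | 100 per arm | 125 per arm |
|---|---|---|
| 0 | 0.732 | 0.829 |
| 0.1 | 0.736 | 0.833 |
| 0.2 | 0.750 | 0.844 |
| 0.3 | 0.774 | 0.864 |

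The 9% end of the range corresponds to r = 0.3. That is about 4 percentage points of power at 100 per arm (0.774 − 0.732).

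**The case against.** The best defence is that nothing in the plan is wrong. Women are randomised 1:1:1, so the interaction test keeps its type I error without baseline*phase, and chance imbalance is already covered by that error rate. Regression to the mean that is common to the three post-baseline phases cancels; only a part that differs by phase could remain, and no figure in the document shows one. The covariate is not idle: it cuts the SE of the group comparison, which the plan also powers. If the planning model's equal correlations extend to baseline, the new term gains nothing. The article is condensed, and a fuller plan may already contain the term. All of this stands, and it limits the point to a recommendation.

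It does not remove the point. The same section writes out the interactions it intends, namely group*phase and group by change in FACT-B. Baseline named simply as a covariate is therefore most naturally read as a main effect, and a better model form is available at almost no cost.

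A reader might infer three stronger things that the document does not support:

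- That baseline was put in to sharpen the interaction test, so the plan fails at its own purpose. No purpose is stated.
- That the primary analysis is simply unadjusted. This is true of one term, with complete data only.
- That correlation with baseline must fall from weeks 1-3 to weeks 7-10, so a gain is assured. No baseline-phase correlation is given.

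**Conclusion.** The point holds as an optional improvement. Under the model as described, with a random intercept and complete phases, baseline BFI leaves the group*phase estimates, SEs and F unchanged. This follows from algebra and needs no assumed correlations. The size of the benefit does need them: nil if baseline correlates equally with the phases, and about 0.25% to 9% of the variance of the mid-to-end contrast over the assumed ranges at an intra-class correlation of 0.5. The term is not required for validity.

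Nor does it address a separate feature of the plan: group*phase compares change among post-baseline phases, not the fall from baseline.

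**What to change.** State the primary model as: phase-average BFI = group + phase + group*phase + baseline BFI + baseline BFI*phase + age, ethnicity and baseline HADS, with the random subject effect. For daytime activity and VAS-F, use that outcome's own baseline and its interaction with phase; the week of Actiwatch-S wear before the baseline visit supplies both.

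The cost is one extra term and two degrees of freedom. At 100 per arm the within-woman degrees of freedom go from 300 × 2 − 2 − 4 = 594 to 592. If the slopes are in fact equal, the SE rises negligibly (0.386 to 0.387-0.388 in the simulated example). No data collection changes. The form should be fixed before arm-level outcome data are seen.

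### A subject random effect is the only within-woman structure stated for the three-phase BFI model; if correlation decays over the ten weeks, the post-hoc phase contrasts are miscalibrated and the primary interaction test slightly inflated

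*Protocol article*

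**What the plan says.** All of this is in the Protocol article, Statistical issues, under Statistics and power analysis.

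- The model is a "mixed-effects regression analysis with average BFI in the three phases as the outcome, phase as the within-subjects factor", with arm as the between-subjects factor and baseline BFI, demographic variables and baseline HADS as covariates.
- Mid-treatment averages three weekly scores (weeks 1-3). End-treatment also averages three: "The second phase comprising of week-4 to week-6 measures". Washout averages four (weeks 7-10), after acupressure has stopped at week 6.
- For dependence within a woman, a subject "random-effect will be used to account for the clustering effect within the three measurements on the same subject". No residual structure, phase-specific variance or robust standard error is named for this model.
- On the main test: "Of primary interest is the group*phase interaction, the significance of which will indicate differences in extent of decrease between the arms".
- On follow-up tests: "Post-hoc analyses of phase difference within each arm will be carried out", with an adjustment for multiple comparisons.
- The promised diagnostics concern distributional assumptions, with transformation as the example remedy. Covariance is not mentioned.

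The actigraphy and VAS-F outcomes use the same analytical framework. The Power analysis section assumes a variance of 4 at all time-points, a subject variance of 4 and an intra-class correlation of 0.5, in a model with two phases.

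**The concern.** A random intercept with independent, equal-variance residuals is compound symmetry: every pair of phases has the same correlation and every phase the same variance. That is a strong assumption here. Weeks 1-3 adjoin weeks 4-6 but are separated from weeks 7-10 by a whole phase, the last phase is off treatment, and it averages four scores rather than three.

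Under this model every phase contrast, and the interaction, uses one pooled residual variance. If the true variance of a change differs between pairs of phases, the pooled value is too large for some contrasts and too small for others. At stake are the level and power of the post-hoc comparisons. Mid-treatment versus washout matters because duration of effect after stopping is a stated secondary interest. A multiplicity adjustment does not correct a wrong standard error.

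**Working it through.** **The plan's own figure.** The article gives no covariance for three phases, so there is no figure to reproduce on this exact point. The nearest is the interaction power of 0.82 at 100 per arm, from the two-phase model. Mean changes of 0, 0 and -1 have a sum of squares about their mean of 2/3. With residual variance 4, the noncentrality is 100 × (2/3) / (2 × 4) = 8.33 on 2 and 297 degrees of freedom, which gives power 0.732 (0.829 at 125 per arm). That gap is a separate matter and does not bear on this point.

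**Inputs.** From the article: averages over 3, 3 and 4 weeks; a subject random effect; a 5% level. Assumed: weekly residual errors within a woman follow AR(1) with autocorrelation ρ, on top of the subject effect. The subject variance and the residual scale cancel from everything below.

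**Formulas.** Let C be the 3x3 covariance of the phase averages and H = I − 1/3 (every element of the subtracted matrix is 1/3).

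- Variance the model assigns to any phase difference: 2s², where s² = trace(HC)/2.
- True variance of the difference between phases p and q: C_pp + C_qq − 2C_pq.
- True level of a nominal 5% test: 2 × [1 − Φ(1.96 × √(model variance / true variance))].
- Omnibus interaction (4 df): level from the corresponding weighted sum of chi-squares.

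The variance ratio is the same for a phase difference within an arm and for a difference between arms in that change.

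**Worked case, ρ = 0.5** (weekly residual variance set to 1). The diagonal of C is 0.6111, 0.6111, 0.5156. The covariances are 0.1701 (mid, end), 0.1367 (end, washout) and 0.0171 (mid, washout). Then s² = 0.4713 and the model variance is 0.9426.

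- Mid-to-end: true variance 0.6111 + 0.6111 − 2 × 0.1701 ≈ 0.882. Ratio 1.069, standard error 3.4% too large, level 4.3%.
- Mid-to-washout: true variance 0.6111 + 0.5156 − 2 × 0.0171 ≈ 1.093. Ratio 0.863, standard error 7.1% too small, level 6.9%.

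**Across ρ:**

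| ρ (assumed) | Mid-to-end | Mid-to-washout | Interaction |
|---|---|---|---|
| 0 | 6.1% | 4.5% | 5.0% |
| 0.2 | 5.5% | 5.1% | 5.0% |
| 0.3 | 5.2% | 5.6% | 5.1% |
| 0.5 | 4.3% | 6.9% | 5.2% |
| 0.7 | 3.1% | 8.8% | 5.6% |
| 0.9 | 1.9% | 11.2% | 6.5% |

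Mid-to-end crosses 5% at ρ of about 0.35. At ρ = 0.9 the model standard error is 19% too large for mid-to-end and 19% too small for mid-to-washout.

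**Check by simulation** (20,000 null trials per case, 100 per arm, RA versus SA contrasts):

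- Exact compound symmetry: 4.8-4.9% for contrasts, 5.0% for the interaction.
- Weekly ρ = 0.8: 2.5% mid-to-end, 10.4% mid-to-washout, 6.0% interaction.
- Weekly ρ = 0.9: 1.9%, 11.2% and 6.6%.
- Phase variances 6, 8, 10 with unequal correlations (also assumed): 0.5-1.8% mid-to-end, 6.3-7.0% end-to-washout, 7.3-9.3% mid-to-washout, 5.4-6.6% interaction.

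**Two phases.** With only two phases and complete data, 2s² = C₁₁ + C₂₂ − 2C₁₂, which is exactly the true variance of the difference, even if the two variances differ. The power model is therefore untouched.

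**The case against.** The article does not say that the residuals are independent, and SAS, which it names, can fit a random effect and a residual structure together. Such detail often sits in an analysis plan, and none is shown. This carries weight against calling the plan wrong. It carries less against suggesting an improvement, because the article does choose a device for the primary model and names no other.

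A reader might infer that the errors on the phase contrasts are simply wrong, in both directions. The documents do not support that. They report no phase covariances. The power section assumes constant variance and a single correlation, from values described as pilot-based estimates, and under those assumptions every test holds its level. The autocorrelation is what remains after the subject effect is removed, so low values are possible. At zero, the 3/3/4 averaging alone makes mid-to-end slightly liberal and mid-to-washout slightly conservative, the reverse of the decaying case.

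A reader might also infer that power for the expected RA effect is lost. The means that place the RA-SA separation between mid- and end-treatment belong to the two-phase power model, where the problem cannot arise with complete data. Only the three-phase analysis could be conservative for that contrast, and only if correlation decays enough.

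**Conclusion.** The point holds as a conditional one and is a minor improvement. As written, the three-phase model allows one variance and one correlation, and the design gives reason to doubt both. If weekly residual autocorrelation lies between 0.5 and 0.9, the mid-to-end test is conservative (down to 1.9%) and the mid-to-washout test liberal (up to 11.2%). The primary interaction test stays near its nominal level, at most about 6.6% in any case tried. The consequence falls mainly on comparisons the plan itself calls post-hoc. The size rests wholly on covariances that the article does not give, and the direction for mid-to-end depends on them too.

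**What to change.** Keep the fixed effects as they are. In place of the subject random intercept, specify an unstructured 3x3 within-woman covariance for the three phase averages, fitted by REML with Kenward-Roger degrees of freedom. State a fallback in advance in case it does not converge, for example the random intercept with robust standard errors. Apply the same wording to the actigraphy and VAS-F models, which share the framework.

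The cost is one or two sentences and four more covariance parameters (six instead of two), negligible with 300-375 women. If compound symmetry does hold, almost nothing is lost.
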